## Abstract

**Background:**

Research suggests that an eight-week Mindfulness-Based Cognitive Therapy (MBCT) program may be effective in the treatment of generalized anxiety disorders. Our objective is to compare the clinical effectiveness of the MBCT program with a psycho-education programme and usual care in reducing anxiety symptoms in people suffering from generalized anxiety disorder.

**Methods:**

A three armed randomized, controlled clinical trial including 9-month post-treatment follow-up is proposed. Participants screened positive using the Structure Clinical Interview for DSM-IV (SCID) for general anxiety disorder will be recruited from community-based clinics. 228 participants will be randomly allocated to the MBCT program plus usual care, psycho-education program plus usual care or the usual care group. Validated Chinese version of instruments measuring anxiety and worry symptoms, depression, quality of life and health service utilization will be used. Our primary end point is the change of anxiety and worry score (Beck Anxiety Inventory and Penn State Worry Scale) from baseline to the end of intervention. For primary analyses, treatment outcomes will be assessed by ANCOVA, with change in anxiety score as the baseline variable, while the baseline anxiety score and other baseline characteristics that significantly differ between groups will serve as covariates.

**Conclusions:**

This is a first randomized controlled trial that compare the effectiveness of MBCT with an active control, findings will advance current knowledge in the management of GAD and the way that group intervention can be delivered and inform future research.

Unique Trail Number (assigned by Centre for Clinical Trails, Clinical Trials registry, The Chinese University of Hong Kong): CUHK_CCT00267

## Background

Generalized anxiety disorder (GAD) is one of the most common mental health problems seen in the primary care or community setting [1] and is associated with significant disability and high utilization of health services [2]. According to established evidence [3], medication or cognitive behavioral therapy are the first line treatments for its management. However, side - effects and costs associated with medications can be barriers to treatments and individual cognitive behavioral therapy can be expensive and time consuming. In addition, for both medication and cognitive behavioral therapy, persistence of residual symptoms continues to be an issue even for those who respond to these treatments initially [2]. As a result, there is a need to use other treatment that falls between a minimalist and intensive approach that can reduce patients' symptoms and health care utilization.

One recently established intervention is mindfulness based cognitive therapy based on mindfulness meditation, modelled after the mindfulness-based stress reduction (MBSR) programme [4] at the University of Massachusetts. Mindfulness refers to "paying attention in a particular way on purpose, in the present moment and non-judgmentally."[4] For example, a mindful approach to one's inner experience is simply viewing "thoughts as thoughts" as opposed to evaluating certain thoughts as positive or negative.

Mindfulness Based Cognitive Therapy (MBCT) (formerly called attentional control) is a theory driven treatment approach developed by Zindel Segal, Mark Williams and John Teasdale with the aim to discover a cost-effective treatment approach to significantly reduce relapse and recurrence of major depression [5]. Cognitive therapy techniques involved in MBCT include education about mood symptoms, the role of negative thoughts, and how rumination, avoidance, suppression, and struggling with unhelpful cognitions and emotions can perpetuate distress rather then resolve it. MBCT emphasizes acceptance rather than change strategies and offers no training in changing the content of thinking but rather seeing thoughts as thoughts rather than as reflections of reality (meta-cognitive awareness) [6]. Recently, MBCT has been suggested as a therapy for treating anxiety symptoms [7] since training in present moment mindful awareness may provide a useful way of responding for individuals with generalized anxiety.

Although it has been shown in randomized controlled clinical trials that MBCT can reduce the likelihood of relapse in people with recurrent episodes of depression [8,9], the evidence for the effectiveness of MBCT in reducing anxiety symptoms among people with anxiety disorder is less well established. So far, three pilot studies, one that employed mixed methodology and studies with a pre and post intervention design have been conducted.

In an exploratory mixed qualitative and quantitative study, Finucane & Mercer [10] showed that the use of mindfulness based cognitive therapy for patients with active anxiety symptoms in primary care was both acceptable and beneficial to majority of patients in his study and more than half of the patients in the study continued to apply mindfulness techniques 3 months after the course had ended. In a study by Evans et al [11] that employed a pre and post intervention (without control) design, they showed that there were significant reductions in anxiety and depressive symptoms post intervention in patients with generalized anxiety disorders. Recently, Yook et al [12] showed that there were significant improvements in Pittsburgh Sleep Quality Index, Penn State Worry Questionnaire, Ruminative Response Scale, Hamilton Anxiety Rating Scale and Hamilton Depression Rating Scale scores at the end of the 8-week program when compared to scores at baseline. However, all these studies were pilot studies with small sample size that ranges from 11-22 participants and with no control group which makes it hard to draw conclusion on the effectiveness of MBCT in treating anxiety symptoms.

## Research objectives

### Primary Objectives

The primary objective of the study is to evaluate the superior effects of MBCT in reducing anxiety symptoms in patients with generalized anxiety disorder from the community and primary care at 9 months when compared to Psycho-Education Group using cognitive behavioural therapy and Usual Care (UG) groups.

### Secondary objectives

The secondary objectives of this study are to evaluate the effects of MBCT on:

• Patients' reduction of worry symptoms post intervention at 9 months

• Patients' reduction of depressive symptoms post intervention at 9 months

• Patients' reduction of the use of psychiatric medication post intervention at 9 months

• Patients' increase in quality of life post intervention at 9 months

• Patients' reduction in use of health service post intervention at 9 months

• Patients' reduction in leave of absence from work post intervention at 9 months

## Methods and Design

The current study protocol was approved by the Joint Chinese University of Hong Kong and New Territories East Cluster (CUHK-NTEC) Clinical Research Ethics Committee (CREC).

This study is a randomized controlled trial with three study arms: the MBCT programme led by trained MBCT instructors, Psycho-Education Group (PEG) using CBT principles led by clinical psychologist, and usual care (UC) which will be offered MBCT at the end of the study for ethical reasons. The MBCT and group PEG consist of eight 2-hour weekly sessions. Outcome measures of all participants will be collected at similar time points (baseline, immediately post intervention, and at 3, 6 and 9 months post intervention). The previous studies that evaluated the effectiveness of MBCT for anxiety did not employed a control group; the inclusion of comparison groups, a usual care group and PEG, will be important in evaluating the benefits of MBCT.

Three instructors with at least two-year experience in teaching MBSR or MBCT will lead the MBCT groups while three clinical psychologists with at least master degree in clinical psychology will be hired for conducting the PEG.

### Participants

Entry criteria for the current proposed study will include all of the followings:

1) being 21-65 years of age; 2) having, at baseline assessment, a DSM-IV TR principal diagnosis of generalized anxiety disorder on SCID (Structured Clinical Interview for DSM-IV) [13] and a score of 19 or above using the Chinese version of the Beck Anxiety Inventory [14]; 3) can understand Cantonese; 4) are willing to attend either the mindfulness based cognitive therapy program or the group cognitive behavioural therapy; 5) if patient is on medication for his/her condition, he or she should be on stable doses of medication for 3 months before starting treatment.

Exclusion criteria will include any one of the followings: 1) illiterate subjects as they will not be able to complete the homework diary; 2) psychiatric and medical comorbidities that are potentially life threatening (i.e. psychosis, suicidal ideation, terminal medical illness) or those expected to severely limit patient participation or adherence (e.g. psychosis, current substance abuse, dementia, pregnancy); 3) those who are currently seeing a cognitive behavioural therapist or psychotherapists/counsellors.

Patients will be recruited from: 1) referral from doctors who work in the General Outpatient Clinics (GOPC) of the New Territories East Cluster of the Hospital Authority and who are interested in this study; 2) review of those who have been referred to be seen by a psychiatrist for anxiety symptoms and who are on the wait list to be seen for at least 12 months (currently there are more than 500 patients in this category with a majority stating that their major complaint is anxiety);. 3) a website set up by the University that provide health-related information which is available to general public.

All interested subjects will be screened on phone by a trained research assistant to determine eligibility in accordance to the pre-set inclusion and exclusion criteria. Those eligible subjects will then be scheduled to have a diagnostic interview with a family physician; the family physician will further confirm the eligibly with the Structured Clinical Interview for DSM-IV SCID [13]. Both the family physician and the research assistant are trained to use the DSM-IV SCID with a psychiatrist. All eligible participants will be seen by the principal investigator (PI) 1-4 weeks before the start of the interventions to further explain the study, to confirm eligibility, and provide informed consent.

A statistician who is not involved in any part of the study independently randomized participants by using a predetermined random table generated by Microsoft Excel 2002. These numbers will not be decoded until the intervention group is assigned.

The allocation is concealed from the researchers, who carries out the baseline assessment or recorded the data, and the statistician who carried out the analysis. The allocation is unknown to the participants until the first appointment.

The research study has been approved by the Joint Chinese University of Hong Kong-New Territory East Cluster (CUHK-NTEC) Ethics Committee.

### Mindfulness Based Cognitive Therapy (MBCT) plus usual care - treatment arm

After an initial individual orientation session, the MBCT program will be delivered by an instructor who has been trained in mindfulness based cognitive therapy and who has more than 2 years of training experience in MBCT. One programme of 18 participants will be conducted for 8 weeks with 2 hours group training sessions. The programme will include daily homework exercises which will include guided (taped) or unguided awareness exercises directed at increasing moment by moment nonjudgmental awareness of bodily sensations, thoughts, and feelings together with exercises designed to integrate application of awareness skills into daily life. Key themes of MBCT include empowerment of participants and a focus on awareness and acceptance of experience in the moment. Participants are helped to develop a "decentred" perspective on thoughts and feelings, in which these are viewed as passing events in the mind.

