### Data and statistical analysis

Baseline characteristics of the three groups will be compared by ANOVA test for continuous variables and chi-square test for categorical variables. The baseline factors will include age, sex, medication status, psychological and lifestyle characteristics. Our primary end point is the change of anxiety and worry score (BAI and Penn State Worry Scale) from baseline to the end of intervention. Secondary outcomes included the change in scores of CES-D and SF-12. For primary analyses, treatment outcomes will be assessed by ANCOVA, with change in anxiety score as the baseline variable, while the baseline anxiety score and other baseline characteristics that significantly difference between groups will serve as covariates. A two-sided P value of 0.05 or less will be considered be statistically significant. For secondary analyses, the three groups will be simultaneously taken into the analysis of variance model for repeated measures. The baseline measurement of anxiety symptoms and any significant secondary outcome variables will be entered into the model as a covariate as they are considered to be confounders. Analysis will also be performed on an "intention to treat" analysis.

Since there have been no studies on MBCT with an active control that control for contact time and attention, we need to use the only available study on GAD with an active control by Wetherell et al [22] for sample size calculation. The null hypothesis for this study is that there will be no improvement in the outcome measures in the MBCT group relative to other groups and we will test this hypothesis using a one-sided analysis.

Assuming that the average change of mean score of BAI of patients in MBCT is 5.6 (7.4), in the discussion group is 2.0 (7.4) and that in usual care control is 1.1(7.4) with a 1-sided type I error of 5% and 80% power to detect statistical significant differences between the MBCT and psycho-education group as well as MBCT and usual care control, the required sample size is 76 subjects in each group. We set our enrolment target at 228 subjects.

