## Discussion

This will be the first study conducted to investigate the usefulness of MBCT using a control group in the treatment of anxiety symptoms in those with generalized anxiety disorder. One of the key strengths of this proposed study when compared to previous studies in this field is the use of an active control group since most of the previous studies have only employed a pre-post design or lack of an active controls.

Since the active control group is conducted by psychologists using CBT principles, which is the current recommended low intensity intervention by the National Institute of Clinical Excellence (NICE) for patients with GAD who suffer from milder symptoms of anxiety in the UK, the results of this trial will advance current knowledge in the management of GAD and the way that group intervention can be delivered and inform future research. One of the advantages of MBCT is the potential for having larger number of participants when compared to normal CBT group (range from 6-8). In this study, we plan to have larger group size than group size previously adopted by previous investigators of MBCT trial.

If MBCT is shown to be effective in reducing participants' symptoms, further economic analysis can be conducted to further evaluate the cost-effectiveness of this intervention. Moreover, it can be further disseminated in various primary and community settings for helping patients with GAD in the community.

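### MBCT and PEG are delivered in therapy groups, but the planned models and sample size treat participants as independent: any positive within-group correlation makes the MBCT–PEG standard error too small

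*Protocol article*

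**What the plan says.** In the protocol article, the section on the MBCT arm states: "One programme of 18 participants will be conducted for 8 weeks with 2 hours group training sessions". With 76 participants in the arm this means several such programmes, and Methods and Design confirms the plural: "Three instructors with at least two-year experience in teaching MBSR or MBCT will lead the MBCT groups". The same section describes PEG as a group programme of eight weekly two-hour sessions, run by three clinical psychologists; its group size is not given. Usual care involves no therapy groups. The Discussion presents size as a merit of MBCT: "we plan to have larger group size than group size previously adopted by previous investigators of MBCT trial".

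The section Data and statistical analysis fixes the model: "For primary analyses, treatment outcomes will be assessed by ANCOVA". The covariates are the baseline anxiety score and any baseline characteristics that differ significantly between arms. The secondary model is a repeated-measures analysis of variance. Neither includes therapy group or leader. The sample size uses mean BAI changes of 5.6, 2.0 and 1.1 with a common SD of 7.4, "with a 1-sided type I error of 5% and 80% power to detect statistical significant differences", and arrives at 76 per arm. The same section sets the significance rule differently: "A two-sided P value of 0.05 or less will be considered be statistically significant".

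**The concern.** Participants who share a room, a leader and eight sessions tend to have correlated outcomes. Here that correlation can arise in two of the three arms, so the design is partially nested. ANCOVA and repeated-measures ANOVA as named take participants as independent. With positive correlation, they understate the variance of an arm mean in proportion to group size, so the larger groups favoured in the Discussion carry a statistical cost that the plan does not recognise.

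The comparison most exposed is MBCT versus PEG, which the Discussion presents as a key strength of the trial. With about four MBCT groups and three leaders, one cohesive group or one strong leader could pass for a treatment effect, and the planned P value would not reflect it.

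**Working it through.** **Inputs from the article.** BAI change differences 5.6 − 2.0 = 3.6 (MBCT vs PEG) and 5.6 − 1.1 = 4.5 (MBCT vs usual care); SD 7.4; 76 per arm; MBCT group size 18.

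**Assumptions, not in the article.** ICC 0.01 to 0.10. PEG group size either 18 (as for MBCT) or 7 (the middle of the 6–8 that the Discussion gives for a normal CBT group). All 76 per arm analysed. No credit is taken for variance removed by baseline adjustment.

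**Step 1, the plan's own figure.** n per arm = 2 × SD² × (z_α + z_β)² / difference².
- MBCT vs PEG, one-sided 5%, 80% power: 2 × 54.76 × (1.645 + 0.842)² / 12.96 = 52.2, so 53.
- The same, two-sided 5%: 66.3, so 67.
- MBCT vs usual care: 34 one-sided, 43 two-sided.

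The stated 76 is not reproduced; it is larger than the inputs require. An unstated dropout allowance would come close: 53/0.70 = 75.7, or 67/0.90 = 74.4. Under independence, 76 per arm gives 91% one-sided or 85% two-sided power against PEG.

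**Step 2, clustering.** Design effect per grouped arm: DE = 1 + (m − 1) × ICC. Usual care has DE = 1. For two equal arms the variance is multiplied by V = (DE₁ + DE₂)/2. Then:
- true two-sided type I error of the unadjusted test = 2 × [1 − Φ(1.960/√V)]
- SE = 7.4 × √(2V/76) = 1.200 × √V
- power of a test using the correct SE = Φ(difference/SE − z_α)

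Example, ICC 0.05 with 18 in both arms: V = 1 + 17 × 0.05 = 1.85 and √V = 1.360. Type I error = 2 × [1 − Φ(1.441)] = 15%. SE = 1.633, and two-sided power = Φ(2.205 − 1.960) = 60%.

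| ICC | V: PEG 18 / PEG 7 / usual care | True type I error (nominal two-sided 5%) | Two-sided power | One-sided power |
|---|---|---|---|---|
| 0.01 | 1.17 / 1.115 / 1.085 | 7% / 6% / 6% | 79% / 81% / 95% | 87% / 88% / 97% |
| 0.02 | 1.34 / 1.23 / 1.17 | 9% / 8% / 7% | 74% / 77% / 93% | 83% / 86% / 97% |
| 0.05 | 1.85 / 1.575 / 1.425 | 15% / 12% / 10% | 60% / 67% / 88% | 71% / 77% / 93% |
| 0.10 | 2.70 / 2.15 / 1.85 | 23% / 18% / 15% | 45% / 53% / 79% | 57% / 66% / 87% |

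In each cell the order is MBCT vs PEG with PEG groups of 18, MBCT vs PEG with PEG groups of 7, and MBCT vs usual care.

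**Step 3, how much clustering 76 per arm absorbs (18 in both arms).** One-sided: 76/53 = 1.434, so ICC = 0.434/17, about 0.026. Two-sided: 76/67 = 1.134, so ICC = 0.134/17, about 0.008. Both need full retention.

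**Step 4, few groups.** 76/18 = 4.2 groups. With four groups in each active arm, the between-group comparison has about 4 + 4 − 2 = 6 degrees of freedom. With a t reference on 6 df and 18 per group, power against PEG at ICC 0.01 is about 79% one-sided and 64% two-sided; at ICC 0.05 it is about 62% and 46%. Smaller PEG groups would give more groups and more degrees of freedom.

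**The case against.** The strongest objection is to the power claim. A reader might infer that power is certainly below 80%. The article does not support that. Its one-sided inputs need only 53 per arm, so at an ICC of 0.01 or 0.02 the one-sided power in the table is still above 80%. This stands, with limits: under the article's own two-sided rule the surplus covers an ICC of only about 0.008; the article does not say that the surplus is for clustering; and its Limitations section expects attrition without giving a rate. A surplus also does nothing for type I error.

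Second, the ICC is wholly assumed. Allocation is by individual, so the correlation arises mainly after randomisation and may lie near the low end, where the error is 6%–7%. This stands for the size, not for the direction under positive correlation.

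Third, groups of 18 in both arms is the less favourable of the two PEG sizes considered. This stands, and both are shown.

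Fourth, MBCT versus usual care is fairly robust: two-sided power stays at 79% or more over the whole range. This stands, although its type I error still rises to 6%–15%.

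Fifth, random effects and degrees-of-freedom methods are often left to an analysis plan, which is not shown here. That would answer a complaint about missing detail. The article, however, names the primary model, its covariates and the sample-size inputs, and those do not fit the group delivery it describes.

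**Conclusion.** The point holds in a conditional form. Both active arms are delivered in groups, and the stated analyses and sample size assume independence. With any positive within-group correlation, the planned MBCT–PEG test is anti-conservative. For an assumed ICC of 0.01–0.10 its true two-sided error is 7%–23% with PEG groups of 18 and 6%–18% with groups of 7.

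For power, the supportable statement is that clustering lowers it by an amount that depends on the ICC, the PEG group size and the alpha used. It may or may not fall below 80%; cluster-level degrees of freedom and attrition both lower the ICC at which it does. The direction is well founded. The size is uncertain because neither the ICC nor the PEG group size is documented. This should be corrected before analysis.

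That 76 does not follow from its inputs, and that the sample size and the significance rule use different alphas, are separate matters, used here only to size the effect.

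**What to change.** - **Primary model.** Replace the ANCOVA with a baseline-adjusted, partially nested mixed model: arm and baseline score as fixed effects, a random intercept for therapy group in the MBCT and PEG arms only, and a small-sample degrees-of-freedom correction.
- **Repeated-measures model.** Carry the same therapy-group term into it.
- **Leader.** Record therapy group and leader for every participant in the active arms, and examine leader in a sensitivity analysis. Three leaders per arm are too few to promise a precise leader variance.
- **Sample size.** State the PEG group size. Restate power in Data and statistical analysis over a range of ICC and PEG group size, under one alpha that matches the analysis.

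**Cost.** Analysis wording, two recorded variables and a somewhat more complex model, with no extra patients. The downside is wider intervals and a less favourable stated power. With about four groups per arm the variance component will be poorly estimated, and the degrees-of-freedom correction can cost power even when the ICC is small: at ICC 0.01 with 18 per group, two-sided power against PEG goes from 79% to about 64% on 6 df.
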